##### Analysis of Secondary Endpoints

For continuous endpoints, the same analysis model will be applied. For binary endpoints, 95% CIs for proportions by treatment groups will be estimated with the Clopper-Pearson method. The proportions of the 2 groups will be compared with Fisher exact test.

#### Safety Analysis

##### Adverse Events and Device-Related Problems

The safety primary endpoints in this study are proportions of adverse events and device-related problems. The number of events and the proportion will be calculated, and 95% CIs for the proportions will be estimated with the Clopper-Pearson method.

#### Sample Size Estimation

The total sample size in this trial was set at 40 patients (20 per group).

##### Rationale

The mean changes from baseline in the FMA at 28 days after study treatment are assumed to be 6.9 and 3.0 in the BMI and control groups, respectively, based on previous clinical studies [57,58]. The SD for the change is also assumed to be 4.0. Under these assumptions, 17 patients per group results in 80% power for testing the between-group difference in means with a two-sided 5% alpha. Taking into account 15% exclusions from the analysis, the target sample size in this trial was set at 20 patients per group (total of 40 patients).

#### Significance Level and Multiplicity

Significance levels for all tests in this trial are set at two-sided 5%, and confidence levels for all interval estimations are two-sided 95%. No multiplicity adjustment will be performed because this study has a single efficacy primary endpoint.

#### Interim Analysis

No interim analysis was conducted in this trial.

#### Change in Original Statistical Analysis Plan

All changes in the original SAP will be reported in the clinical study report for this trial.

#### Statistical Analysis Plan

The SAP for this study, which contains comprehensive details of data handling and statistical analysis methods, will be finalized before unblinding of this study.

### Ethics and Dissemination

This study was conducted in accordance with Ministerial Ordinance on Good Clinical Practice for Medical Devices [59]. All participants provided voluntary written informed consent. Prospective participants were fully informed about what study participation involved and the potential benefits and risks. Ethics approvals had been obtained from the institutional review board of Keio University (protocol number: KCTR-D008, reference number: D16-03). In addition, for Saiseikai Kanagawa-ken Hospital, Tokyo Metropolitan Rehabilitation Hospital, and Tokyo Bay Rehabilitation Hospital, ethics approval had been obtained from the institutional review board of Saiseikai Kanagawa-ken Hospital (protocol number: KCTR-D008). Any protocol amendments will be submitted for ethical approval and communicated to the trial registry. The results of this study will be used to gain regulatory approval for the manufacture and sale of the medical device used in this study in Japan. After approval, the results will be presented at scientific meetings and published in journals.

## Results

Recruitment started in March 2017 and ended in July 2018. This trial is currently in the data correcting phase. This RCT is expected to be completed by October 31, 2018.

## Discussion

This multicenter RCT was designed to demonstrate the effect of EEG-BMI training compared with simple mental imagery on upper extremity function, including finger function, in poststroke patients with severe impairment of finger function. Although several neurorehabilitation approaches have shown clinically important improvements in arm function of poststroke, hemiparetic patients, no intervention is widely accepted as effective treatment for improving finger function [7,16-18]. If this device is approved for manufacturing and sale by the Japanese government, it will be the first neurorehabilitation product targeting improvement of finger function. Clinically and scientifically, the results of this RCT will provide significant knowledge about the contribution of sensorimotor feedback to motor learning and recovery in poststroke patients compared with open-loop imagery.

Several studies have reported the effectiveness of rehabilitation using other BMI systems for chronic stroke patients with upper extremity paresis [58,60-63]. However, no device is approved as an official medical device. In addition, this trial will demonstrate that closed-loop sensory-motor feedback training with the EEG-BMI rehabilitation system can induce functional recovery and that this improvement will be maintained or will increase 4 weeks after the intervention, because the primary outcome is the change in FMA between baseline and follow-up 4 weeks after the end of the intervention. If rehabilitation induces plastic changes in the brain of chronic stroke patients, acquired recovery will be sustained or will increase in the several weeks following the intervention. On the other hand, the recovery will decrease if the effect of rehabilitation is transient. In this study, the control intervention is based on open-loop motor imagery training without any feedback. Therefore, the results of this RCT will provide several important suggestions about the mechanisms of the effect of closed-loop sensory-motor feedback training on neural plasticity in the damaged brain by comparing closed-loop feedback training using the EEG-BMI system with dose-matched, open-loop motor imagery training. This is a unique scientific point of view in this RCT compared with other studies of BMI rehabilitation.

In this RCT, we assess a sufficient number of functional measures of the upper extremity (such as ARAT, MAL, motor score of SIAS, and MAS), subjective satisfaction with the treatment (GAS), ADL (BI), and QOL (SS-QOL) to make the outcome of this RCT comparable with those of other trials. In addition, electrophysiological assessments (surface EMG and EEG during BMI training) will be adopted to elucidate the underlying mechanisms of improvement with BMI rehabilitation.

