#### Outcome Measurement

#### Schedule of Assessment

The primary outcome measure was assessed by a blinded evaluator. Other functional measurements were assessed by evaluators who were trained by the organizer of this RCT. Most assessments were conducted at baseline, after intervention (post), and 4 weeks after intervention (follow-up). EEGs were recorded by the EEG-BMI rehabilitation system during each training session. The schedule of assessments is shown in Table 1.

**Table 1 table1:** Schedule of assessments.

Time points and measure		Baseline	Intervention (10 sessions during 2 weeks)	Posttreatment	Follow-up (4 weeks after treatment)

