#### Efficacy Analysis

##### Analysis of the Primary Endpoint

The primary endpoint of this trial is a change from baseline in the FMA at 28 days after study treatment. The superiority of the BMI group compared with the control group in terms of the primary endpoint will be demonstrated by means of an analysis of covariance model, which contains the baseline as a covariate and treatment group as a factor. Least squares means for the changes in treatment groups will be estimated and compared between the 2 groups. Missing data at 28 days after study treatment will be handled by multiple imputation, Rubin, which assumes missing at random as the missing data mechanism [56]. The details of the imputation model in the multiple imputation will be described in the SAP before the unblinding.

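### A positive primary result cannot show that the improvement is maintained or increases after treatment, because the change from baseline to follow-up does not use the post-treatment score

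*Protocol article*

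**What the plan says.** The claim is in the Discussion of the protocol article. The trial is expected to demonstrate that closed-loop training induces recovery, and the text adds: "this improvement will be maintained or will increase 4 weeks after the intervention, because the primary outcome is the change in FMA". The change meant there runs from the baseline visit to the 4-week follow-up. The following sentences explain what is at issue. Plastic change in the brain would show as recovery that holds or grows in the weeks after training, while "the recovery will decrease if the effect of rehabilitation is transient".

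The analysis is fixed under Analysis of the Primary Endpoint: "The primary endpoint of this trial is a change from baseline in the FMA at 28 days after study treatment". It is tested with "an analysis of covariance model, which contains the baseline as a covariate and treatment group as a factor". Under Analysis of Secondary Endpoints, "For continuous endpoints, the same analysis model will be applied".

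Under Schedule of Assessment, "Most assessments were conducted at baseline, after intervention (post), and 4 weeks after intervention (follow-up"). Table 1 shows the FMA scored by the blinded evaluator at all three visits.

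**The concern.** Whether a gain is kept, grows or fades after treatment is a question about the path from the end of treatment to follow-up. The Discussion frames it that way itself, by contrasting sustained with decreasing recovery. It then rests the answer on an endpoint that spans baseline to follow-up and skips the visit in between.

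A reader who follows the stated reasoning would take a significant primary result as evidence of durability. The same result would arise if the BMI arm had gained much more by the end of training and then lost a large part of it, which is the transient pattern the Discussion wants to rule out. The Ethics and Dissemination section says the results are meant to support regulatory approval and publication, so an unsupported durability statement could carry into both.

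**Working it through.** **Inputs.** From the sample size Rationale: mean changes at 28 days "are assumed to be 6.9 and 3.0 in the BMI and control groups, respectively"; "The SD for the change is also assumed to be 4.0"; 17 per group for 80% power at two-sided 5%; 15% exclusions; target 20 per group. Not given in the article, and therefore assumed below: the BMI-arm change at the post-treatment visit, and the SD of the post-to-follow-up change.

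**Step 1: the plan's own figure.** The difference is 6.9 − 3.0 = 3.9. By the normal approximation, n per group = 2 × (1.960 + 0.842)² × 4.0² / 3.9² = 16.5, so 17. Power at 17 is 81.1% (normal) or 78.7% (exact t). Inflation gives 17 / 0.85 = 20. The stated sample size reproduces.

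**Step 2: does the primary test respond to the post-treatment score?** Hold the follow-up means at 6.9 and 3.0 and the SD at 4.0, and vary the BMI-arm change at post. Later change = 6.9 − post; share retained = 6.9 / post.

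| BMI change at post (assumed) | Post to follow-up | Retained at follow-up | Power, n = 17 (t / normal) |
|---|---|---|---|
| 5.0 | +1.9 | 138% | 78.7% / 81.1% |
| 6.9 | 0 | 100% | 78.7% / 81.1% |
| 10.9 | −4.0 | 63% | 78.7% / 81.1% |
| 13.8 | −6.9 | 50% | 78.7% / 81.1% |

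The last column is constant because the post-treatment score is in neither the outcome nor the model. These powers are for a plain two-group comparison of changes. Adjusting for baseline may shift their level, but it does not bring in the post-treatment visit. The post-treatment score might enter the multiple imputation model for missing 28-day values, which the article leaves to the SAP. That would help fill in follow-up scores and would still not compare the two visits.

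**Step 3: would a direct estimate be informative?** Assume an SD of 3 to 4 points for the post-to-follow-up change. An SD of 4 corresponds to an SD of 4.0 for the change from baseline at both visits with a correlation of 0.5, since 4.0 × √(2 × (1 − 0.5)) = 4.0; a higher correlation gives a smaller SD.

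- Within the BMI arm, the 95% half-width is t(0.975, n − 1) × SD / √n. At n = 20: 2.093 × 3 / 4.472 = 1.4 and 2.093 × 4 / 4.472 = 1.9. At n = 17: 2.120 × 3 / 4.123 = 1.5 and 2.120 × 4 / 4.123 = 2.1.
- Between arms, it is t(0.975, 2n − 2) × SD × √(2/n). At n = 20: 1.9 to 2.6. At n = 17: 2.1 to 2.8.

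So the BMI-arm change after treatment could be estimated to within roughly 1.4 to 2.1 points, against an assumed gain of 6.9.

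**The case against.** **The sentence may mean only that benefit is still present at 4 weeks.** The primary endpoint could show that. But the same clause also claims a possible increase, which needs an end-of-treatment reference, and the sentences that follow contrast sustained with falling recovery. The milder reading does not fit.

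**The fault is in the Discussion, not in the hypothesis or test.** This stands. The objectives, the primary analysis and the sample size do not make maintenance a success criterion, and the error rate and power are untouched. The point concerns what may be concluded.

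**The comparison may be in the SAP.** This also stands in part. A reader might infer that no post-to-follow-up comparison is planned at all. The documents do not support that: the article defers full analysis detail to an SAP that is not shown, so one can say only that the article describes none. The faulty inference remains either way, because the Discussion gives the primary outcome as its sole reason.

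**Other stronger readings also fail.**

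- A reader might infer that the whole plasticity argument rests on this endpoint. The Discussion bases its mechanistic suggestions on the contrast between closed-loop and open-loop training, and adds EMG and EEG measures; only the durability statement is exposed.
- A between-arm advantage that halves, say from 8 to 4 points, would not show fading in the BMI arm, since controls could have gained 4 points while BMI patients held steady. Within-arm and between-arm changes must be kept apart.
- The 3.2-point minimal detectable change cited under Primary Outcome Measure may look like a ready margin. It is 46% of the assumed BMI gain (3.2 / 6.9) and 82% of the assumed treatment difference (3.2 / 3.9), so it would allow a claim of maintenance without excluding loss of nearly half the gain. Even that loss could be excluded at n = 20 only if the observed mean loss were below about 1.8 points (SD 3: 3.2 − 1.4) or 1.3 points (SD 4: 3.2 − 1.9).

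**Conclusion.** The concern holds as a fault of inference. A positive primary result would show a between-group difference in FMA change 4 weeks after treatment. It would not show that the improvement was kept or grew from the end of treatment. With the follow-up values fixed at the article's planning assumptions, the chance of a positive result is the same under later gain, full maintenance or loss of half the BMI-arm gain.

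That conclusion follows from the structure of the endpoint and does not depend on the assumed post-treatment values, which only illustrate it. The precision figures do depend on the assumed SD of 3 to 4. The validity of the primary test and the sample size are not in question. The matter is worth correcting because the durability statement could enter regulatory and published reports, and the data needed to test it are already collected.

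**What to change.** Either of two changes cures the problem.

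1. Before unblinding, prespecify as a secondary analysis the post-to-follow-up change in FMA, within the BMI arm and between arms, each with a 95% confidence interval. State in advance the largest mean loss still compatible with maintenance and justify it clinically and statistically. Claim maintenance only if the BMI-arm interval excludes a larger loss, and claim an increase only if the interval lies above zero. Report the between-arm contrast alongside, as a separate question. If the SAP already contains this analysis, point the Discussion to it in place of the primary outcome.
2. Otherwise, reword the Discussion so that the primary endpoint supports only a between-group difference present 4 weeks after the intervention, and remove the statement that it demonstrates maintenance or further gain.

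The first option costs one additional secondary analysis and some SAP text. The second costs a sentence. Neither needs new visits, patients or measurements.

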## Appendix

Multimedia Appendix 1 Peer-review report from the Japan Agency for Medical Research and Development (Part 1).

Multimedia Appendix 2 Peer-review report from the Japan Agency for Medical Research and Development (Part 2).

Multimedia Appendix 3 Translation of the peer-review report from the Japan Agency for Medical Research and Development (Part 1).

Multimedia Appendix 4 Translation of the peer-review report from the Japan Agency for Medical Research and Development (Part 2).

## Abbreviations

ADL: activities of daily living
AHA: American Heart Association
AMED: Agency for Medical Research and Development
ARAT: Action Research Arm Test
ASA: American Stroke Association
BI: Barthel Index
BMI: brain-machine interface
CIMT: constraint-induced movement therapy
EEG: electroencephalogram
EMG: electromyography
ERD: event-related desynchronization
FAS: full analysis set
FMA: Fugl-Meyer assessment
GAS: Goal Attainment Scale
HANDS: hybrid assistive neuromuscular dynamic stimulation
IVES: integrated volitional electrical stimulator
JGM 2015: Japanese guidelines for the management of stroke 2015
LDA: linear discriminant analysis
MAL: Motor Activity Log-14
MAS: Modified Ashworth scale
MCID: minimal clinically important difference
NEMS: neuromuscular electrical stimulation
PPS: per protocol set
RCT: randomized controlled trial
RFE: repetitive facilitative exercise
SAP: Statistical analysis plan
SIAS: Stroke Impairment Assessment Set
SS-QOL: Stroke-Specific Quality of Life Scale
tDCS: Transcranial direct current stimulation
2D: two-dimensional
UE: upper extremity
